##### Focus group

All healthcare professionals (physiotherapists, occupational therapists, psychologists and psychiatrists) who were involved in the care of patients allocated to the intervention arm will be invited to take part in a focus group within 4 weeks of the end of the trial. We aim to invite 6–10 healthcare professionals for the focus group,^26^ which will last approximately 60 min. Focus groups will take place at the hospital and several potential dates will be offered so those invited will have the opportunity to attend the one most convenient to them. Although our preference will be to conduct focus groups in person, they might also be conducted virtually through an online platform in light of any COVID-19 or similar restrictions. We do not expect staff to attend more than one session, but they would be welcome to attend another session if they have additional feedback to contribute.

#### Usage of additional healthcare resources

The usage of additional healthcare resources will be collected through all participants’ self-reported questionnaires at the 6-month follow-up.

#### Staff costs and main resources to implement the CCM

The staff costs and main resources used for the intervention arm will be estimated from the number, type and duration of appointments performed by the case manager, therapists and mental health specialist. Data will be collected using the therapies appointment booking system.

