### Interventions

#### Collaborative care model – intervention arm

The CCM involves three professionals: a physical healthcare provider (physiotherapist or occupational therapist), a mental healthcare provider (psychologist or psychiatrist) and a case manager working closely with the participant. In this trial, the case manager will work with the participant to screen, identify, coordinate and target mental health support according to their individual needs. This will involve:
developing a personalised care plancoordinating appointments with a psychologist or psychiatrist, if requiredmonitoring monthly progress using validated questionnaires first administered at baselineadjusting support needs accordinglycoordination of hospital appointments to reduce missed appointments and burden to the participantstreamlining communication between physical and mental healthcare professionals via email or internal referralsprovision of case manager care alongside routine physiotherapy or occupational therapy (usual care).

Participants will continue to be seen by a physiotherapist or occupational therapist as usual. Even if the participant is not seen again by the musculoskeletal specialist after a single visit, the case manager remains involved in the patient's care. The case manager can alert the musculoskeletal specialist to deterioration or lack of improvement in the participant's musculoskeletal condition, as well as refer participants for psychological or psychiatric support that provides more responsive input.

Participants who are randomised to the intervention group will be notified at the beginning of the trial that they will have a case manager only for the duration of the study. This will be clearly outlined during the consent process.

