#### Usual care – control group

A physiotherapist, occupational therapist or both will assess the participants’ needs to help them work towards individualised goals that are important to them. These professionals will also inform, educate and empower participants to self-manage their physical capacity where possible. Following this initial assessment, participants will have a plan outlining their subsequent therapy, and exercises will be progressed as appropriate. Therapy will most often involve one-to-one sessions, but there may be instances where the participant will be involved in group classes. Physical therapy involves exercises and education; occupational therapy focuses on practical strategies to perform daily tasks. If the therapist identifies a need for additional mental health support, this will be requested via the GP or via an internal referral to the mental health services within the RNOH Trust, as per usual care.

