#### Concomitant healthcare

Concomitant healthcare access for mental and musculoskeletal conditions that was not scheduled will be collected at 6 months from all participants (examples include GP appointments, specialist visits, accident and emergency department visits and other types of support, e.g. chiropractor or osteopath).

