#### Quantitative data

Owing to the exploratory nature of this feasibility study, the sample size will be based on the pragmatic limits of recruitment. Since the primary aim of this study is to determine the feasibility of conducting a future RCT, a descriptive analysis will be performed to examine key feasibility and process-related outcomes. All quantitative data will be uploaded into SPSS^27^ for analysis, where recruitment, retention and follow-up rates at study completion will be quantified using absolute and relative frequencies and percentages of the overall population.

In particular, the percentage of potential participants who agree to undergo the screening assessment out of the total number of potential participants who were initially invited will be calculated. The percentage of the total number of participants who were enrolled into the study out of the total number invited will be calculated with a 95% confidence interval ±6%.

The main analysis will estimate the percentage of potentially eligible participants, consent and overall uptake. The retention, follow-up and outcomes rates will be calculated in relation to the number recruited. Engagement with the intervention will be described by the percentage of appointments attended as a proportion of booked appointments. An estimated engagement rate of approximately 90% (32/36 retained patients) will give a 95% confidence interval width of ±10%. Additional healthcare resources will be described by type and frequency of use in absolute numbers.

The means and confidence intervals of clinical outcomes will be calculated to determine their sensitivity to change. This will guide the identification of a primary outcome measure for a future RCT. In addition, we will determine the acceptability of the clinical outcomes by calculating percentage rates of completion for the PHQ-ADS, EQ-5D-3L, NPRS, PDI, MSK-HQ and the GRoC.

A detailed statistical analysis plan will be developed by the study statistician. To illustrate participant flow, we will report results using a CONSORT flow diagram.^23^

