#### Cost analysis

The objective of the cost analysis will be to assess the relative cost of the clinical staff from the number, type and duration of appointments performed by the case manager, therapists and mental health specialist. Costs will be calculated using the National Cost Index^30^ for the NHS.

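### Staff cost is built only from intervention-arm appointments, so case-manager work outside appointments is left out and the undefined relative cost has no costed usual-care counterpart

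*Protocol article*

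**What the plan says.** Among the secondary outcomes, the protocol article (Primary and secondary outcomes) lists an estimate of the staff cost of delivering the intervention. Two later sections say how this will be done.

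- **Staff costs and main resources to implement the CCM** fixes the arm and the unit: "The staff costs and main resources used for the intervention arm will be estimated from the number, type and duration of appointments". Three staff groups are counted: case manager, therapists and the mental-health specialist. On the source, the section says: "Data will be collected using the therapies appointment booking system".
- **Cost analysis** words the aim differently: "The objective of the cost analysis will be to assess the relative cost of the clinical staff from the number, type and duration of appointments". The same three staff groups are named, and a national NHS cost index supplies the prices.

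Three other places bear on what those data can show.

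- **Collaborative care model – intervention arm** describes the case manager's tasks, several of them coordination and communication. It adds: "The case manager can alert the musculoskeletal specialist to deterioration or lack of improvement in the participant's musculoskeletal condition". It also says that participants go on seeing their physiotherapist or occupational therapist as they otherwise would.
- **Usual care – control group** allows mental-health input for controls. Where a therapist sees a need, "this will be requested via the GP or via an internal referral to the mental health services within the RNOH Trust".
- **Concomitant healthcare** is the resource item taken from both arms: "Concomitant healthcare access for mental and musculoskeletal conditions that was not scheduled will be collected at 6 months from all participants".

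**The concern.** The article fixes one arm, one unit (appointments performed) and one data source for costing. These choices do not fit its own account of the intervention in two respects.

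First, what distinguishes the model from usual care is the case manager, and part of that role takes place between appointments. A count of appointments with their durations gives that part no cost.

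Second, the costed staff include therapists whose appointments both arms receive, and mental-health specialists whom controls can also reach. Without the same counts in usual care, the intervention-arm total mixes the model's cost with the cost of routine care, and a *relative* cost has no between-arm basis if that is what the word means.

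The trial is meant to guide a definitive multicentre trial. A staff cost that omits part of the new role, and cannot be set against usual care, is a weak basis for planning that trial's resources. Minutes spent on email, referrals and alerts cannot be recovered reliably later if they are not recorded at the time.

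**Working it through.** The documents give no cost, hours or unit price, so there is no plan figure to reproduce. The check sets the sections side by side and then uses symbols only to establish the direction of error.

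**1. Which case-manager work is an appointment?** The intervention section lists seven elements.

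| Element | Outside an appointment by its wording? |
|---|---|
| Personal care plan | Not necessarily; may be done with the participant |
| Arranging psychology or psychiatry appointments | Yes |
| Monthly monitoring by questionnaire | Not necessarily |
| Adjusting support | Not necessarily |
| Coordinating hospital appointments | Yes |
| Communication between professionals by email or referral | Yes |
| Case-manager care alongside routine therapy | Not necessarily |

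Three of seven are coordination or communication by their wording. The alerts and referrals described in the next paragraph of that section add to these. A count of elements is not a share of time, and no share of time is given.

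**2. Direction of error in the case-manager component.** Let A be the cost of the case manager's appointments and N the cost of the work outside them. The full component is A + N and the plan captures A, so the shortfall is N. N is above zero if the role is carried out as described. Its size is unknown.

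**3. Can the time added by the model be isolated?** Let T be therapist cost and M mental-health specialist cost, with subscripts for the collaborative care (c) and usual care (u) arms.

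- The plan yields T_c + M_c + A.
- The staff cost added by the model is (T_c − T_u) + (M_c − M_u) + A + N.
- Plan minus added cost = T_u + M_u − N.

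The plan costs none of T_u, M_u and N. The first two push the total above the added cost and the third pushes it below. So only the case-manager component has a known direction of error. The error in the total, read as added cost, has no determinable sign.

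**4. Could other planned data supply T_u and M_u?**

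- The 6-month self-report covers all participants but is limited, in the Concomitant healthcare section, to care that was not scheduled. An appointment made after an internal referral could be read as scheduled and so left out.
- Engagement with appointments is a feasibility indicator that is not limited to one arm. The Quantitative data section says: "An estimated engagement rate of approximately 90% (32/36 retained patients) will give a 95% confidence interval width of ±10"%. Thirty-six retained patients exceed the 20 in one arm, so some attendance data from usual care appear intended. Nothing links them to costing or to mental-health contacts.

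**The case against.** The strongest reply is that the secondary outcome asks only for the staff cost of delivering the intervention, which needs no comparator, and that the costing section matches it. The word *relative* appears without a reference, and since three staff groups follow it, cost across staff types is an equally good reading. This stands: a reader might infer that the article promises an incremental cost between arms and then fails to collect it, but no section states that aim. What remains is an undefined word, together with the fact that therapist appointments are counted although participants would have them anyway.

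A reader might also infer that control-arm mental-health care goes entirely unrecorded. The documents do not support that. The 6-month questionnaire covers mental conditions in both arms. Its examples include GP and specialist visits, which are commonly booked, so the restriction to unscheduled care may mean care outside the planned therapy. Two other sections (Follow-up assessments; Usage of additional healthcare resources) repeat the item without that restriction. The wording is ambiguous; the data are not shown to be absent.

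Nor can one say that the bulk of the case manager's work is missed, or put a multiple on the cost. Care planning, monitoring and adjustment may happen in contacts, and any share of time would be pure assumption. It would also bear on the case-manager component alone, not on total staff cost.

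Finally, an article condenses a fuller protocol, which might describe an activity log. That is possible. But the article does not merely stay silent: it names the unit and the source, and those as stated do not cover the work outside appointments.

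**Conclusion.** The point holds in two parts.

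1. Followed as written, the plan understates the case-manager component of the staff-cost outcome, by an amount the documents do not allow to be calculated. This assumes that the case manager does the described work outside appointments and that the booking system is the only source.
2. The Cost analysis section leaves *relative* undefined, and no usual-care staff contacts are to be costed. Therapist and mental-health time added by the model therefore cannot be separated from usual care. This holds on either reading of the word; the lack of a between-arm figure is a failure against a stated aim only if *relative* was meant between arms.

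The outcome is secondary and descriptive, and no co-primary feasibility outcome is affected. The change is still worth making, because the missing minutes have to be recorded as they occur.

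**What to change.** - Have the case manager keep a short per-participant log of non-appointment minutes (coordination, email, referrals, alerts), and cost it together with the appointments. State this in the section on staff costs and main resources.
- Run the same extraction of therapist, psychology and psychiatry appointments for usual care, cost it by the same rules and report staff cost descriptively by arm, with no test. If no between-arm view is wanted, delete *relative* from the Cost analysis section, or say that it means across staff types.
- In the Concomitant healthcare section, make clear that mental-health contacts reached by referral count even if scheduled.

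The cost is a few minutes of logging per contact, one more extraction from an existing system and a small wording change to the 6-month questionnaire.

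### Staff cost is built only from appointments performed, so unfilled missed slots carry no cost and the cost of delivering collaborative care may be understated

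*Protocol article*

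**What the plan says.** The costing unit is fixed in two places in the protocol article. In the data-collection section on staff costs, the intervention arm's cost is to be "estimated from the number, type and duration of appointments performed by the case manager, therapists and mental health specialist". Under Cost analysis, the objective is to "assess the relative cost of the clinical staff from the number, type and duration of appointments performed by the case manager" and the same other staff. The source is named: "Data will be collected using the therapies appointment booking system". So is the source of prices: "Costs will be calculated using the National Cost Index" for the NHS.

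Three other sections bear on this:

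- Primary and secondary outcomes lists, as a secondary outcome, an estimate of the staff cost needed to deliver the intervention.
- The description of the intervention arm includes, among the case manager's tasks, coordinating hospital visits so that fewer are missed.
- Quantitative data defines engagement as the "percentage of appointments attended as a proportion of booked appointments", so booked and attended counts are both to be collected.

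**The concern.** Delivering a service requires staff time to be reserved. When a patient misses a booked slot and nobody else is seen in it, the time has been used, but a cost built from performed appointments records nothing. The plan expects some appointments to be missed, because it sets engagement below 100% and gives the case manager the job of reducing misses. The cost measure cannot register the quantity that this task is meant to change.

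At stake is the staff-cost figure that this feasibility trial would hand to the planners of the definitive trial. If it omits lost time, the resources needed to run collaborative care could be budgeted too low.

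**Working it through.** **Inputs**

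- Costing unit: appointments performed, intervention arm (Staff costs and main resources to implement the CCM; Cost analysis).
- Engagement: attended over booked, expected at about 90%, written as 32/36 = 88.9% (Quantitative data).
- Planned size: 40 participants, 20 per arm (Sample size).
- Share of missed slots that are lost: not given, so varied below.
- Whether the unit costs already include non-attendance: not given.

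**Step 1. Reproduce the plan's own figure.** The article gives no cost figure. The only stated number near this point is the precision of engagement: "An estimated engagement rate of approximately 90% (32/36 retained patients) will give a 95% confidence interval width of ±10" per cent. The usual half-width is 1.96 × √(p(1 − p)/n) with n = 36.

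- p = 0.90: 1.96 × √(0.90 × 0.10/36) = 0.098, or 9.8 points.
- p = 32/36: 1.96 × √(0.889 × 0.111/36) = 0.103, or 10.3 points.

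The stated ±10% reproduces.

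**Step 2. What 32/36 can and cannot tell us.** The fraction counts retained patients, whereas the definition beside it counts appointments. Its denominator of 36 also exceeds the 20 patients in one arm, so it cannot describe the costed arm alone. The 90% used below is an illustration and not the protocol's missed-slot rate; the protocol gives no such rate.

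**Step 3. Size of the possible understatement.** Let a be the attendance rate and f the share of missed slots that are lost, meaning neither refilled nor used for other work. Take slots of equal cost, and unit costs that do not already include non-attendance. Per booked slot, performed time is a and lost time is f(1 − a). The rise needed in the performed-only cost is

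rise = f(1 − a)/a.

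For 100 booked slots at a = 0.90, 90 are performed and 10 are missed. If all 10 are lost, the cost should be 100/90 = 1.111 times the recorded one. If 5 are lost it is 95/90 = 1.056, and if none are lost it is 90/90 = 1.

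| Attendance a | f = 1 | f = 0.5 | f = 0 |
|---|---|---|---|
| 0.95 | 5.3% | 2.6% | 0% |
| 0.90 | 11.1% | 5.6% | 0% |
| 32/36 | 12.5% | 6.3% | 0% |
| 0.80 | 25.0% | 12.5% | 0% |

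If the unit costs already spread non-attendance over attended visits, the rise is 0% in every cell, and adding missed slots would count them twice.

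**Step 4. Is the missing information obtainable?** Engagement needs booked and attended counts, and the cost data come from the booking system. Slot outcome should therefore be available from a source already in the plan.

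**The case against.** The strongest reply is that this is a costing convention, time delivered against time reserved, and that the handling of non-attendance belongs in the full protocol or the analysis plan that the article says will follow. It can be added that attendance will be reported anyway, so a reader could scale the performed-only cost by it, and that the estimate is secondary and descriptive in a 40-patient trial with no hypothesis testing. Much of this stands. It limits the importance of the point, and it means that making booked slots the sole main figure would be debatable. It does not remove the point, because the article is not silent: it chooses performed appointments as the unit, twice. Nor would one overall attendance rate let a reader rebuild the cost well, since misses may differ between case manager, therapist and mental health contacts of different length and price.

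A reader might go further and infer that better attendance under collaborative care would show up as extra cost against usual care. The documents do not support that. The data-collection section costs the intervention arm only. The relative cost in the Cost analysis section has no named comparator and may mean relative across the staff groups it lists. Any figure for such a comparison would need a usual-care attendance rate that the protocol does not give, and equal bookings in both arms, although the intervention arm adds contacts by design.

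It would also be too strong to say that the costing hides the one saving the model is meant to produce. Fewer missed visits is part of one item in a longer list of case manager tasks, and the Discussion names other hoped-for gains.

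**Conclusion.** The point holds in a conditional form. As written, staff time held for booked but missed slots counts as zero, which does not sit well with the objective of costing delivery, and the delivery cost may be understated. If attendance were about 90%, the recorded cost would need to rise by about 11% with every missed slot lost, 5.6% with half lost, and 0% with all refilled or with unit costs that already absorb non-attendance. The documents state neither condition and give no slot-level missed rate, so these figures show a range and are not an estimate of the error. The consequence is confined to the cost estimate carried to the future trial.

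**What to change.** In Staff costs and main resources to implement the CCM and in Cost analysis, state that all booked slots will be extracted from the booking system with their outcome: attended, missed or cancelled late. Report the number and staff cost of missed slots separately, and give the intervention-arm delivery cost both without and with them. Add missed slots only where the unit cost does not already include non-attendance, and say which is the case for the unit costs used. While that text is open, say what the relative cost is relative to.

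The price is one extra field from a source already in use, with no added burden on participants, and a somewhat higher upper figure for delivery cost. The upper figure will be too high where missed slots were in fact refilled, which is why both figures should be shown.

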### Sample size

As this study is a feasibility trial, all analyses will be descriptive, with no hypothesis testing. Consequently, no formal sample size calculation has been conducted. We aim to recruit 40 patients in total, with 20 randomised to each arm.

The study aims to recruit these patients over 3 months, with a target recruitment rate of 20% of all eligible patients. It is estimated that there may be at least 200 new eligible patients in 3 months. Assuming this number of eligible patients, the recruitment rate could be estimated within ±6% with a 95% confidence level.

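### The planned staff cost is an intervention-arm total that includes usual-care therapy, so it cannot show what adding collaborative care costs

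*Protocol article*

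**What the plan says.** The last secondary outcome in the protocol article (Primary and secondary outcomes) is an estimate of what it costs in staff to deliver the intervention. The section that implements it is headed as the staff costs and resources needed to implement the CCM. It states: "The staff costs and main resources used for the intervention arm will be estimated from the number, type and duration of appointments", and the appointments counted are those "appointments performed by the case manager, therapists and mental health specialist". The source is the therapies appointment booking system.

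The Cost analysis section lists the same three staff groups and sets the objective to "assess the relative cost of the clinical staff from the number, type and duration of appointments". It names no comparator for the word relative.

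The section on the intervention arm describes therapy in two ways. It includes the therapist in the model: "The CCM involves three professionals: a physical healthcare provider (physiotherapist or occupational therapist". It also places case-manager care beside routine therapy, which it labels usual care, and says: "Participants will continue to be seen by a physiotherapist or occupational therapist as usual". The control-group section gives participants physiotherapy, occupational therapy or both, and allows mental health support to be requested through the GP or "via an internal referral to the mental health services within the RNOH Trust, as per usual care".

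**The concern.** The outcome and the section heading present the figure as the cost of delivering or implementing the CCM. The counting rule produces something else: the cost of all listed staff contact in the intervention arm, including therapy that the same article says goes on regardless of allocation. Nothing in the article subtracts that therapy or sets it against a control-arm figure.

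The secondary outcomes are meant to show the model's potential for real-world use, and the Discussion says the findings will guide a definitive multicentre trial. A service deciding whether to add a case manager needs the cost over and above what it already pays for. An intervention-arm total does not answer that. It also moves with the amount of therapy the musculoskeletal problem requires, whatever the CCM itself consumes.

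**Working it through.** The article gives no cost, unit price or appointment count, so there is no stated figure to reproduce. The check compares the sections and then writes out what the rule measures.

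**Text comparison**

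| Question | Protocol article | Section |
|---|---|---|
| What is the target? | Staff cost of delivering or implementing the CCM | Primary and secondary outcomes; heading of the staff-cost section |
| Which arm is costed? | Intervention arm only | Staff costs and main resources to implement the CCM |
| Whose appointments count? | Case manager, therapists, mental health specialist | Same section; Cost analysis |
| What is therapy in that arm? | Routine usual care, and also one of the three CCM roles | Collaborative care model – intervention arm |
| Do controls get therapy? | Yes | Usual care – control group |
| Can controls get mental health input? | Yes, via the GP or internal referral | Usual care – control group |
| Is control-arm staff time costed? | Not stated | – |

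Self-reported resource use does not fill the last row. It is collected from all participants at 6 months, but the Concomitant healthcare section limits it to care that was not scheduled. Routine therapy sessions of controls are therefore not captured there.

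**What the rule measures**

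For the mean cost per participant, let M be the case manager, T1 and S1 the therapists and mental health specialist in the intervention arm, and T0 and S0 the same two groups in the control arm.

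- Planned figure = M + T1 + S1
- Added staff cost of the CCM = M + (T1 − T0) + (S1 − S0)
- Planned figure − added cost = T0 + S0

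The gap is the control arm's own staff cost, for which the article states no costing.

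**Illustration of size (assumed, not from the documents)**

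Let s = T1 / (M + T1 + S1) be the therapists' share of the planned figure. Suppose therapy use is equal in the arms (T1 = T0) and controls have no specialist cost (S0 = 0). Then planned / added = 1 / (1 − s):

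- s = 20%: 1 / 0.80 = 1.25
- s = 50%: 1 / 0.50 = 2
- s = 80%: 1 / 0.20 = 5

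Specialist referrals in the control arm (S0 > 0) would raise the ratio. Extra therapist use caused by the CCM (T1 > T0) would lower it.

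**Would deleting the therapists be enough?**

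That gives M + S1, and (M + S1) − added cost = S0 − (T1 − T0). It is still wrong whenever controls are referred for mental health support or the CCM changes therapist use. The article gives routes for both: the internal referral quoted above, and "The case manager can alert the musculoskeletal specialist to deterioration or lack of improvement". The case manager also coordinates appointments with the aim of fewer being missed.

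**The case against.** The strongest reply is that the protocol itself defines the CCM as involving three professionals, one of them the therapist, and that the rule counts exactly those three. On that definition, therapist time belongs in the figure. Neither the outcome nor the staff-cost section calls the figure additional or incremental. This stands. A reader might infer that the protocol makes an inclusion error and that its CCM cost is overstated. The documents do not support that, because they never say the figure is an added cost, and as a total for the intervention arm it is correct.

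A second reply is that the relative cost in the Cost analysis section could mean cost by staff group, in which case therapy would appear on its own line, or cost between arms, in which case routine therapy would largely cancel. Either is possible. The first would make therapy visible but would still not remove mental health input that usual care also provides. The second needs control-arm appointment data, and the data-collection section specifies only the intervention arm.

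A third reply is that presentation by staff group can be left to the full protocol or to the announced statistical analysis plan. That is fair for layout. However, the article does fix the arm, the staff and the data source, and these determine which quantity can be estimated.

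Finally, this is one descriptive secondary outcome in a 40-patient feasibility trial, and no co-primary outcome depends on it. That limits the weight of the point.

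**Conclusion.** The point holds as a mismatch between a label and a quantity. The figure is presented as the staff cost of delivering or implementing the CCM, but the stated rule gives the total staff cost of care in the intervention arm, including therapy that the article calls usual care. With no stated control-arm costing and no comparator for the relative cost, the plan as written cannot say what adding the CCM costs.

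The excess, when the total is read as an added cost, equals the staff cost of usual care. Its size cannot be derived from the documents. The ratios of 1.25 to 5 rest wholly on assumed therapist shares of 20% to 80%, equal therapy use in both arms and no specialist cost among controls. They show only that the gap could be modest or several-fold. The issue should be corrected, but it does not affect the feasibility outcomes.

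**What to change.** In the staff-cost section and the Cost analysis section:

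1. Extract the same booking-system data (how many appointments, of what kind and how long) for both arms.
2. Report cost by staff type: case manager, therapist, mental health specialist.
3. Give the added staff cost of the CCM as the between-arm difference in mean cost per participant, with a confidence interval and no test. This fits the statement that "all analyses will be descriptive, with no hypothesis testing", and it supplies the missing comparator.
4. Show the intervention-arm total separately, labelled as a total that includes usual-care therapy.

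Comparing the arms is better than marking individual therapist contacts as prompted by the CCM. Such marking would be an unmasked judgement and would miss better attendance at routine sessions. The comparison also captures changes in therapist use and mental health referrals under usual care. Referrals that go through the GP to outside services would not be in the hospital's booking system, and the report should say so.

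The cost is a small extra data extraction for 20 control participants, with no added patients or visits. The difference will be imprecise. With 20 per arm and a common standard deviation, the 95% half-width is about 2.02 × √(2/20) = 2.02 × 0.316 = 0.64 standard deviations of cost per participant. It should be reported as descriptive.
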